**Methods:**

Women (age ≥18 years) who were followed up at the women’s HIV clinic of an academic medical center, with a recent history of nonadherence to HIV care (missed appointments, unsuppressed viral load, or not taking medications as prescribed), will be enrolled. The experimental arm will receive the intervention, which includes health reminders and psychoeducational messaging, plus clinical standard of care reminders. The psychoeducational messaging will target patient-level barriers of HIV stigma and medical mistrust and resilience as a patient-level strength. The control arm will receive standard of care reminders only (ie, mailed appointments and automated telephone calls). All aspects of the study and intervention will be offered in the participants’ preferred language. The primary outcome is the feasibility and acceptability of the study. The secondary outcomes are changes in self-reported medication adherence, depression symptoms, HIV stigma, medical mistrust, resilience, and clinic attendance and viral suppression extracted from the participants’ medical records. Data will be assessed at baseline (T0) and 2 subsequent clinic visits—approximately 3 to 4 months from the baseline (time 1; T1) and 6 to 9 months from the baseline (time 2; T2). Qualitative data will be transcribed and analyzed iteratively. Bivariate analyses will compare data by the study group (chi-square, odds ratios, and t tests). Exploratory analyses will be conducted for each outcome variable—T1 and T2 values will be compared with values at T0 by the study group.

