### Trial Design

This is a concurrent, two-phase, mixed method, pilot randomized controlled trial. Both the qualitative and quantitative components collect data from the target population women living with HIV. The trial begins with the qualitative component.

#### Phase 1

The qualitative component comprises interviews in the form of participant focus groups and participant key informant sessions.

#### Phase 2

The quantitative component is a short-term longitudinal intervention, where participants will be randomized to 1 of 2 study arms (parallel group). The allocation ratio is set at 1:1. The control arm will receive the standard of care for reminders, and the experimental arm will receive the intervention, in addition to the standard of care for reminders (see Study Comparators section). Data will be collected at baseline (T0), 3 to 4 months postbaseline (time 1; T1), and 6 to 9 months postbaseline (time 2; T2) after the launch of the intervention (exploratory trial).

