### Eligibility Criteria

The following are the eligibility criteria for the study: (1) women aged ≥18 years; (2) confirmed HIV diagnosis (per the clinic’s standard); (3) active patient (ie, not withdrawn, transferred, or dismissed); (4) 2 or more previously scheduled visits 12 months before the study enrollment; and (5) nonadherence, based on 1 or more of the following criteria: missed 1 or more visits, having a viral load >20 copies/mL, or not taking HIV antiretroviral medications as prescribed.

Participants will have to confirm at the time of enrollment that they possess a working mobile phone number (to receive text messages). We will exclude women with serious psychiatric diagnoses, who are cognitively impaired or are not able to consent for themselves.

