**Secondary outcomes**								
	**Clinical outcomes**							
		Adherence to medication		Wilson 3-item self-report measure for medication adherence (self-administered) [16]		Continuous (score); range 1-100		Participant (T0, T1, and T2)
		Clinic attendance (change)		Number of missed visits 1 year before assessment (T0), between T0 and T1, and between T1 and T2		Continuous (number)		Electronic medical record
		Viral suppression		Viral load		Categorical; ≥20 copies/mL or <20 copies/mL		Electronic medical record or measured through a blood test (T0, T1, and T2)

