### Study Outcomes

The primary and secondary outcomes are summarized in Table 1. Data will be collected either from the electronic medical record (EMR), the HIV database, or directly from the participants’ responses to questionnaires. For analysis, all outcomes (Table 1) will be reported as a change from baseline. As this is a pilot study, our intention is to determine the most sensitive measures. We will explore the data to determine the most suitable categorizations for a future study; therefore, the total scores will be reduced to categories once all data have been compiled. To report on the participant characteristics, sociodemographic data, including age, race/ethnicity, HIV or AIDS status, socioeconomic status, pregnancy status, substance use, and mental health history (past year), will be collected at T0.

Clinical outcomes (at T0, T1, and T2) that will be examined include a comparative history of self-reported medication adherence, visit attendance, and viral suppression reported as the biological marker of HIV viral load (copies/mL). Psychological and behavioral data include depressive symptoms, internalized stigma, resilience, and medical mistrust (Table 1).

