##### Exploratory Analyses

We will conduct exploratory analyses, where analysis of variance (ANOVA) models will be constructed for each outcome variable. Statistically significant baseline characteristics, mHealth usage, clinically relevant characteristics, and total instrument score will be entered as covariates. The ANOVAs will compare T1 and T2 outcomes to values at T0 by the study group. At T1 and T2, clinical and behavioral outcomes will be compared with values at T0 for both study arms.

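### Within-arm change from T0 is biased toward apparent improvement for the three clinical outcomes that also define eligibility, and the plan does not say that the between-arm comparison carries the inference

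*Protocol article*

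**What the plan says.** Eligibility Criteria requires "nonadherence, based on 1 or more of the following criteria: missed 1 or more visits, having a viral load >20 copies/mL". The third way to qualify is "not taking HIV antiretroviral medications as prescribed". One criterion is enough. The same section requires "2 or more previously scheduled visits 12 months before the study enrollment", which gives the visit criterion its natural window. No window is given for viral load or for medication-taking. The Abstract (Methods) describes the three criteria together as a recent history.

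Table 1 lists three secondary clinical outcomes: self-reported medication adherence, clinic attendance, and viral suppression cut at 20 copies/mL. Attendance is defined as "Number of missed visits 1 year before assessment (T0), between T0 and T1, and between T1 and T2". The four behavioral outcomes are depressive symptoms, stigma, medical mistrust and resilience.

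Study Outcomes says that "all outcomes (Table 1) will be reported as a change from baseline". Exploratory Analyses plans ANOVAs that set T1 and T2 against T0 by study group, and then adds: "At T1 and T2, clinical and behavioral outcomes will be compared with values at T0 for both study arms". The covariates listed there include baseline characteristics that differ significantly, mHealth usage, clinically relevant characteristics and a total instrument score with no time point attached.

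**The concern.** If women are chosen because a fluctuating measure was recently poor, that measure will on average be better next time, treated or not. The three entry variables are also three of the seven secondary outcomes, so their change from T0 contains this regression to the mean in both arms. A before-after gain in the intervention arm would then partly reflect how the women were selected.

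This matters even in a pilot with feasibility and acceptability as its primary outcomes. Power Analysis says that effect sizes will be estimated at the end of the study, Study Outcomes says that the most sensitive measures will be identified, and Conclusions looks ahead to a larger trial. Judging sensitivity by change from T0 would favor the measures used for entry, and effect sizes taken from within-arm change would be too large.

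**Working it through.** The protocol gives no effect size, standard deviation or expected change, so there is no figure of its own to reproduce. The inputs below marked as assumed are not in the document.

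**1. Overlap of entry variables and outcomes**

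| Entry criterion | Secondary outcome | Overlap with the T0 value |
|---|---|---|
| One or more missed visits (12-month visit window) | Missed visits in the year before T0 | Near-direct |
| Viral load >20 copies/mL | Suppression, cut at 20 copies/mL | Same variable, entry window not stated |
| Not taking medication as prescribed | 3-item self-report score | Same construct, entry instrument and window not stated |
| None | Depression, stigma, mistrust, resilience | Indirect only |

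**2. Missed visits among women who entered through a missed visit, no treatment effect**

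Let k be scheduled visits a year, p the mean chance of missing one, and ICC the between-woman intraclass correlation. All three are assumed. Recruitment Strategy gives about 50 patients seen weekly and about 900 women a year, so 50 × 52 / 900 = 2.9 attended visits per woman. Scheduled visits would be 2.9/(1 − p), which is 3.6 at p = 0.2 and 4.8 at p = 0.4. The range k = 3-6 covers this.

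With ICC = 0, the mean at T0 given at least one miss is kp/(1 − (1 − p)^k), and the next year's mean is kp. The relative fall is therefore (1 − p)^k.
- k = 3, p = 0.2: 0.8³ = 0.51 (1.23 missed visits falling to 0.60).
- k = 6, p = 0.4: 0.6⁶ = 0.05 (2.52 falling to 2.40).

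With ICC = 0.3, a beta-binomial with a = p(1/ICC − 1) and b = (1 − p)(1/ICC − 1) replaces the binomial.

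| k | p = 0.2, ICC 0 | p = 0.2, ICC 0.3 | p = 0.4, ICC 0 | p = 0.4, ICC 0.3 |
|---|---|---|---|---|
| 3 | 51% | 27% | 22% | 15% |
| 4 | 41% | 21% | 13% | 10% |
| 5 | 33% | 17% | 8% | 8% |
| 6 | 26% | 14% | 5% | 6% |

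These are falls in a yearly count. Raw counts over the shorter T0-T1 interval would be lower again for a reason unrelated to regression: with a 3.5-month window, 3.5/12 = 29% of the yearly expectation.

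**3. Dilution by the any-one-of-three rule**

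Target Sample Size gives about 20 women per language, so 20 × 3 / 2 = 30 per arm. A simulation with no treatment effect selected women if any of three measures was poor at T0 (assumed test-retest correlation 0.5-0.8, correlation between traits 0-0.3).
- If about 80% of women would qualify, the entry measures improve by 0.02-0.11 SD.
- If about half would qualify (test-retest 0.5 and 0.7), they improve by 0.08-0.21 SD.
- A measure not used for entry, linked to the others only through stable traits, changes by about 0.00 SD.
- A within-arm test at two-sided 0.05 on an entry measure rejects in 5-19% of trials.
- The between-arm test of change rejects in 4.2-5.4%, close to nominal.

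**4. Value of adjusting for T0**

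With equal variance σ² at both times and correlation ρ, the change-score variance is 2σ²(1 − ρ) and the T0-adjusted variance is σ²(1 − ρ²). The ratio is (1 + ρ)/2, which is 0.65 at ρ = 0.3 and 0.85 at ρ = 0.7 (both assumed).

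**The case against.** The strongest reply is that the randomized comparison is already planned. The sentence just before the one on both arms sets T1 and T2 against T0 by study group, and in a 1:1 randomized trial the shared regression cancels there. This stands. A reader might infer that the plan lacks a between-arm contrast, or that the contrast is biased by selection, and the document supports neither. What remains is that the within-arm comparison is stated as an analysis in its own right and nothing says which comparison carries the inference. Cancellation also presumes covariates fixed before randomization, and the covariate list includes mHealth usage, which arises afterwards.

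A reader might also infer that every outcome is affected, or that women were nonadherent at T0 itself. Four of the seven secondary outcomes are not entry variables, and selection is on recent history, so overlap with the T0 value is close to certain only for missed visits.

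A third tempting reading is that significance in one arm but not the other will be taken as an effect. No such rule is stated; the P<.05 cutoff appears under Descriptive Statistics, for baseline differences. Nor should a large figure be attached to it. If both arms truly changed by an equal 0.3-0.5 SD, exactly one of two arms of 30 would reach P<.05 in 37-50% of trials, but that change is assumed, not produced by regression. With the regression-only rejection rates of 0.05-0.19, 2p(1 − p) gives about 10-31%.

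Finally, the analyses are labeled exploratory and exact model terms may sit in a statistical analysis plan not shown. Both points lower the stakes. Adjustment for T0 is a gain in precision, since an unadjusted comparison of change is also unbiased under randomization.

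**Conclusion.** The point holds in a limited form. For missed visits, viral suppression and medication adherence, change from T0 within an arm is biased toward apparent improvement, in both arms. The direction follows from the document; the size does not. Among women who entered through a missed visit, the fall in yearly missed visits with no treatment effect is about 5-50% over the assumed ranges. The top end needs only three scheduled visits a year and no stable differences between women. Across all entrants the shift per measure is about 0.02-0.21 SD under the simulation's assumptions, which may be hard to see with 30 per arm. The comparison by study group is free of this bias, but the protocol does not make it the basis for inference and does not clearly name each outcome's own T0 value as a covariate.

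**What to change.** In Exploratory Analyses, state that inference, and the effect sizes carried to the future trial, rest on the between-arm difference at T1 and at T2 for each outcome, adjusted for that outcome's T0 value and for language (the stratification factor), with a 95% CI. State that within-arm changes are shown descriptively, without P values, and are not called effects. Align the change-from-baseline sentence in Study Outcomes with this.

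The cost is wording only. T0 values and language are already collected, and the sample size, visits and procedures are unchanged.

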##### Statistical Analysis: Missing Data

For individual statistical tests, only records with complete data will be included in the analyses.

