### Intervention Fidelity

#### Laboratory Data

If participants miss their scheduled clinical appointment, they will be asked to come to the clinic’s research wing, where a blood sample will be drawn by a clinical research staff member to obtain the viral load. Quantitative data will be collected as well. This procedure will ensure adherence to study data points T1 and T2.

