#### Quantitative Data Analysis

##### Data Preparation

###### Sociodemographic and Clinical Data

Participants’ mobile numbers will be matched to the mHealth texting system logs; participants’ medical record number (MRN) will be matched to the Ryan White Care Ware database and the hospital’s EMR. Inconsistent data and outliers will be reviewed. Missing data and unresolved data discrepancies will be considered and recorded as *missing data* and excluded from the analyses.

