### Strengths and Limitations

The most significant strength of this study is that, to our knowledge, it is the first HIV adherence intervention in the United States that is designed for minority women across multiple cultural and linguistic contexts. We recognize that the most significant limitation of the study is that there may not be sufficient power to test complex interaction models for the quantitative arm of the analyses. Furthermore, because the intervention is being tested among a cohort of women with a history of nonadherence, study retention may be negatively impacted.

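### Women with no viral load at T1 or T2 are excluded from the suppression analysis, so suppression may be overstated and a retention-driven difference diluted

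*Protocol article*

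**What the plan says.** The exclusion rule appears twice in the protocol article. Under Statistical Analysis: Missing Data: "For individual statistical tests, only records with complete data will be included in the analyses". Under Sociodemographic and Clinical Data: "Missing data and unresolved data discrepancies will be considered and recorded as *missing data* and excluded from the analyses". Neither place makes an exception for viral load.

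Table 1 lists viral suppression as a secondary outcome with two values, "Categorical; ≥20 copies/mL or <20 copies/mL", and no category for an absent result. Its source is the electronic medical record or a blood test, at T0, T1 and T2.

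Laboratory Data (under Intervention Fidelity) gives a recovery route: "If participants miss their scheduled clinical appointment, they will be asked to come to the clinic’s research wing". Research staff then take blood there for a viral load measurement. The section concludes: "This procedure will ensure adherence to study data points T1 and T2".

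Strengths and Limitations notes that, because the women have a history of nonadherence, "study retention may be negatively impacted". No retention, recovery or suppression rate is given anywhere.

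**The concern.** The recovery route is a second request to attend, made to a woman who has just not attended. It will retrieve some viral loads, but it cannot guarantee them, and the limitations section concedes that retention is at risk. A woman who misses both occasions and has no in-window value in the record leaves the analysis.

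Eligibility requires recent nonadherence, and missed visits are one qualifying criterion. The intervention is meant to reduce nonadherence. A woman who has stopped attending is plausibly less likely to be suppressed than one who attends, so dropping her raises the measured proportion in her arm. If the arms lose different numbers of women, the between-arm difference moves too.

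This matters for estimation more than for significance. Power Analysis says the pilot will estimate effect sizes and judge how sensitive the measures are, and Conclusions says a larger trial will build on the findings. A diluted estimate could make suppression look like an insensitive measure.

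**Working it through.** **The plan's own figure.** Target Sample Size gives about 20 women per language, half to control: 20 / 2 = 10 per language per arm, matching Assignment to Study Arms. Three languages give 10 × 3 = 30 per arm, 60 in all. There is no power, dropout or suppression figure to reproduce.

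**Assumed inputs (none is in the document).**
- R, share still in care at the time point: 70% control, 90% intervention.
- s, suppressed among those in care: 60% in both arms.
- r, share of lapsed women whose viral load is obtained by the recall draw: 0 to 100%.
- Lapsed women are unsuppressed (relaxed below).

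**Formulas.**
- Complete-case suppression = R·s / (R + (1 − R)·r)
- All randomised, missing counted as not suppressed = R·s

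**All randomised.** Control 0.70 × 0.60 = 42%; intervention 0.90 × 0.60 = 54%; difference 12 points at every r.

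**Complete case.**

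| r | Control | Intervention | Difference (points) |
|---|---|---|---|
| 0 | 0.42/0.700 = 60.0% | 0.54/0.900 = 60.0% | 0 |
| 25% | 0.42/0.775 = 54.2% | 0.54/0.925 = 58.4% | 4.2 |
| 50% | 0.42/0.850 = 49.4% | 0.54/0.950 = 56.8% | 7.4 |
| 75% | 0.42/0.925 = 45.4% | 0.54/0.975 = 55.4% | 10.0 |
| 100% | 42.0% | 54.0% | 12.0 |

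At r = 0 the analysis holds 21 and 27 women of 30 per arm.

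**Other values.** With s from 50% to 70% and retention of 60/80% or 70/90%, the all-randomised difference is 10 to 14 points. The complete-case analysis keeps none of it at r = 0, 35–42% at 25%, 62–69% at 50% and 83–88% at 75%.

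**Equal retention (70% in both arms).** No difference is lost, but at r = 0 each arm reads 60% against 42%, 18 points too high.

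**Lapsed women partly suppressed.** If 10% to 30% of them are suppressed, the true difference falls from 10 to 6 points. Complete case still shows 0 at r = 0. At r = 50% it shows 6.2 points where the true figure is 10, and 3.7 where it is 6.

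**The reverse case.** Suppose 60% of unmeasured women are suppressed too, so that missingness is unrelated to the outcome. The true difference is 0 and complete case is right. Counting missing as not suppressed reports 54% − 42% = 12 points that do not exist.

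**Precision.** At 30 per arm the standard error of 54% − 42% is √(0.54 × 0.46/30 + 0.42 × 0.58/30) ≈ 0.128, or 12.8 points. Power for that comparison is about 15%.

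**The case against.** A reader might infer that women who drop out of care have no T1 or T2 viral load, that suppression is measured only in those who stayed, and that any benefit on retention is erased. The documents do not support this. Laboratory Data provides a draw for women who miss the appointment, and Table 1 accepts both that draw and the record. Clinic attendance is a separate secondary outcome, counted as missed visits from the medical record, so a benefit on attendance can show without any viral load. In the illustration, full loss of the difference needs zero recovery, and the zero there follows from assuming equal suppression among retained women in both arms. A reader might also infer that the comparison would favour control. That needs a further assumption about the extra women retained by the texts, for which the document gives no basis.

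The strongest objection is to the remedy. One missed visit is enough for eligibility, so a nonadherent woman may well be suppressed. Two-way texting might also bring intervention women to draws without changing suppression. Counting missing as not suppressed would then manufacture a difference, as the reverse case shows. This stands, and it is why neither analysis should be reported alone.

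Stakes are limited. Suppression is secondary and exploratory, the primary outcomes are enrollment and message opening, and sampling error is as large as the illustrated bias. A separate analysis plan could add sensitivity analyses. It would, however, have to depart from a rule stated here twice and without exception.

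**Conclusion.** The point holds in a limited form. Women who miss both the visit and the recall draw, with no in-window value in the record, are excluded, and no analysis treats or examines them as unsuppressed. In this cohort that may overstate suppression in each arm and dilute a difference that works through retention.

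Under the assumed values the loss is 12 points of 12 with no recovery, 4.6 (12 − 7.4) at half recovery and 2.0 at three-quarters. These sizes rest on unequal retention, on lapsed women being less often suppressed, and on equal suppression among the retained. With equal retention only the arm-level rates are affected. If missingness is unrelated to suppression there is no bias. The primary outcomes are untouched. The reason to act is that the pilot intends to carry effect estimates forward.

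**What to change.** 1. In Statistical Analysis: Missing Data, exempt viral suppression from the complete-record rule. Use every viral load that falls in the T1 or T2 window, from the record or the recall draw, whether or not the questionnaires are complete. This also covers the adjusted models. Exploratory Analyses enters total instrument score as a covariate and Study Measures sets incomplete instruments to missing, so a measured viral load could be dropped there. An unadjusted comparison would not be affected.
2. Report suppression at T1 and T2 by arm with all randomised women as the denominator and missing counted as not suppressed, beside the complete-case proportion. Read the two together as a range across assumptions. The first is the floor for each arm's rate; the second is not a ceiling, and the pair does not strictly bound the difference.
3. In Laboratory Data, replace the assurance about T1 and T2 with a statement that the procedure aims to obtain those data. Commit to reporting by arm how many viral loads came from a visit, came from recall, or were missing.

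The cost is a few sentences, one more table row and a short count table. The downside is that counting missing as not suppressed misclassifies women suppressed under care elsewhere and can create a difference when missingness is unrelated to suppression. The complete-case row beside it exposes this.
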